### MRI data analysis

Data preprocessing was carried out using the Statistical Parametric Mapping software package (Statistics Parameter Mapping 12.0, SPM12) (http://www.fil.ion.ucl.ac.uk/spm) (Tavares et al., 2020) and the Data Processing Assistant for Resting - State fMRI (DPARSF) based on the Matlab R2014b platform (Mathworks Inc., Sherborn, MASS). The preprocessing mainly included removing the first 10 time points, slice timing correction, head motion correction (Realign), spatial normalization, detrending, and noise filtering.

### Whole - brain functional activity regional homogeneity analysis

#### Regional homogeneity calculation

The Regional Homogeneity (ReHo) method was employed (Ji et al., 2020), assuming that there were similar changes in the same time series between the selected voxel and its adjacent voxels. In this study, the regional homogeneity of each voxel and its 26 adjacent voxels in the same time series was calculated point - by - point using the DPARSF software package. The Kendall’s Coefficient Concordance (KCC) was used to represent the ReHo value of the selected voxel and its neighboring voxels in the same time series, and a whole - brain ReHo map was generated for each subject (Zhu et al., 2020). Then, non - brain tissues were removed using a whole - brain template, and only the voxels within the template were included in the next step of analysis. To standardize the ReHo values, the ReHo value of each voxel was divided by the mean ReHo value of the whole brain. To ensure that the image data had the properties of a random Gaussian field to meet the statistical assumptions of SPM, spatial smoothing was performed after calculating the ReHo values. The data were smoothed using a Gaussian kernel function with a Full - Width at Half - Maximum (FWHM) of 6 mm to reduce spatial noise and minimize errors introduced during the spatial normalization process.

### Regional homogeneity analysis

SPM12 was used to conduct a regional homogeneity analysis of the resting - state imaging data. First, a paired t - test was used for the comparative analysis of the ReHo images of the APE subjects in each group before and after treatment. Meanwhile, to avoid noise data outside the brain tissue in the results, BrainMask_61 × 73 × 61. img was selected as the whole - brain mask file. The statistical threshold was set at P < 0.005, and the minimum activation cluster was required to be larger than 20 voxels. The results of the regional homogeneity changes in the brain regions before and after treatment were obtained respectively.

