**Methods and analysis:**

This is a randomized, blinded interventional trial with four parallel groups. A total of 84 eligible participants will be randomly assigned to one of four groups: the paroxetine group, CHSGS group, CHSGS + paroxetine group, or placebo group. The primary outcomes are Intravaginal ejaculatory latency time (IELT) and Pre- and post-treatment brain fMRI scans. The Secondary Outcomes include Premature ejaculation profile (PEP), Chinese Index of Premature Ejaculation (CIPE) and TCM syndrome score.

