Therefore, in this protocol, we plan to perform a double-blind randomized controlled trial, aiming to:1. Compared with the placebo and paroxetine, CHSGS will be as the same effective to the treatment for APE.2. Compared with paroxetine alone, CHSGS and combination of drugs will be more effective due to its specific effects.3. Investigate the influence of paroxetine or/and CHSGS capsule treatment on the brain activities of patients with APE compared with that of placebo treatment by fMRI and analyze the possible correlations between the changes of cerebral activity and the improvement of clinical variables in each group so as to explore how the paroxetine and CHSGS capsule manages depression by modulating brain function to treat APE.

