## Methods

### Study design

This study will be a blinded interventional trial with four parallel groups and a natural control group. The study will be conducted in accordance with the Declaration of Helsinki and follows the Consolidated Standards of Reporting Trials statement for randomized trials, as well as the Standard Protocol Items: Recommendations for Interventional Trials (SPIRIT). The trial has been registered with the International Traditional Medicine Clinical Trial Registry (Registration No. ITMCTR2025000309) and Ethics Committee of Chongqing Hospital of Traditional Chinese Medicine (Registration No. 2023-ky-87), and will be proceeded in the Departments of Urology and Radiology at Chongqing Traditional Chinese Medicine Hospital in Chongqing, China. According to the minimum requirements for network analysis of functional neuroimaging studies, 15 subjects were needed in each group, and 21 subjects were included in each group to ensure the credibility of the study results, taking into account the unavailability of data due to patient dropout and head movement during scanning (Desmond and Glover, 2002). Through previous studies and in combination with the actual situation of the project (Rodríguez Del Águila and González-Ramírez, 2014), a total of 84 subjects were included in this study, and they will be equally divided into the following four groups: paroxetine group; CHSGS group; CHSGS + paroxetine group; placebo group. In addition, we will recruit 15 healthy volunteers as natural control group (Figure 1).

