## Discussion

In this protocol study, qualified participants are requested to adhere to their existing living habits and sexual behaviors. Particular attention should be paid to diet, exercise, and sleep quality. Simultaneously, they must complete relevant questionnaires during the entire observational period. To meet the requirements of the Ethical Code and minimize performance - induced biases, all other clinical procedures remain unchanged.

Based on current records and the results of recent randomized controlled trials, paroxetine has a lasting effect and is a favorable option for both patients and their partners in the treatment of APE (Zhang et al., 2019). Nevertheless, the central mechanism underlying its action remains unclear. Given the crucial role of the brain in APE, we have devised a randomized controlled MRI trial to uncover the central mechanism by which paroxetine treats APE (Gao et al., 2022). In this study, we will compare the alterations in brain function following the administration of three interventions: paroxetine, the CHSGS capsule, and combination therapy.

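### The only test specified for the fMRI primary outcome is before/after within each arm, which does not match the placebo comparison promised in aim 3

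*Protocol article*

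**What the plan says.** The abstract of the protocol article makes imaging a primary endpoint: "The primary outcomes are Intravaginal ejaculatory latency time (IELT) and Pre- and post-treatment brain fMRI scans". The Primary outcome section repeats this, naming change from baseline in brain MRI alongside IELT.

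Aim 3, at the end of the Introduction, has two parts. The first is comparative: the influence of paroxetine and/or CHSGS "on the brain activities of patients with APE compared with that of placebo treatment by fMRI". The second is to "analyze the possible correlations between the changes of cerebral activity and the improvement of clinical variables in each group".

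The Regional homogeneity analysis section then fixes the test: "a paired t - test was used for the comparative analysis of the ReHo images of the APE subjects in each group", before versus after treatment. It adds a mask, a threshold (P < 0.005, clusters above 20 voxels) and one output, the before/after changes. Sidedness is not stated.

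The Discussion says "we will compare the alterations in brain function following the administration of three interventions", and lists paroxetine, CHSGS and the combination. It gives no test and does not name placebo there. The Study design section adds that "we will recruit 15 healthy volunteers as natural control group".

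**The concern.** A before/after change inside one arm combines the drug effect with placebo response, repeat-scan effects and natural course. Randomisation and the placebo capsules separate these only if the arms are compared directly. Four paired tests give four lists of changed regions. A region listed for CHSGS and not for placebo invites the conclusion that CHSGS changed it, but one significant and one non-significant result is not a test of their difference.

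At stake is one of the two primary outcomes. If the section is followed as written, regional effects could be attributed to CHSGS or paroxetine without a controlled comparison, in a trial that has the placebo arm and the scans needed to make one.

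**Working it through.** **1. The plan's own figure.** Four arms of 21 give 4 × 21 = 84, as stated. The Study design section takes 15 evaluable per arm as the minimum and enrols 21, an implied allowance of 1 − 15/21 = 28.6%. No effect size, SD or power is given, so the calculations below use n = 15 and n = 21 with assumed effects.

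**2. Aim against analysis.**

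| Element of aim 3 | Analysis stated for the images |
|---|---|
| Active arms versus placebo | None; only paired tests within each arm |
| Correlation of brain change with clinical change, within group | Not blocked by the missing placebo contrast. The Pearson analysis names only clinical scores |

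The independent-samples t-test, analysis of covariance and generalized estimating equations all stand under Clinical variables analysis and are not tied to the ReHo maps.

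**3. What side-by-side reading does.** Take one region with the same true change δ in both arms, so there is no drug effect; δ is in units of the SD of the before/after change. With independent arms and two-sided P < 0.005:

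- p = P(|T| > t at 0.9975 with n−1 df), where T is noncentral t with noncentrality δ√n. For example, δ = 0.5 and n = 21 gives 0.5 × √21 = 2.29 and p = 0.231.
- Chance that a given active arm is significant and placebo is not = p(1−p). In the same example, 0.231 × 0.769 = 0.178.

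| Shared change δ | p, n=15 | p(1−p), n=15 | p, n=21 | p(1−p), n=21 |
|---|---|---|---|---|
| 0 | 0.005 | 0.5% | 0.005 | 0.5% |
| 0.3 | 0.036 | 3.5% | 0.059 | 5.6% |
| 0.5 | 0.129 | 11.2% | 0.231 | 17.8% |
| 0.7 | 0.320 | 21.8% | 0.534 | 24.9% |
| 1.0 | 0.698 | 21.1% | 0.906 | 8.6% |

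(Products use unrounded p.) If P < 0.005 is read as one-sided, the values at δ = 0.5 are 15.7% (n = 15) and 21.7% (n = 21), and at δ = 0.7 they are 24.5% and 23.0%. A direct between-arm test at two-sided P < 0.005 declares a false difference in 0.5% of cases per contrast, whatever the shared change.

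**4. Price of the direct test.** For a two-sample t-test on change, power uses noncentrality Δ√(n/2) with 2n−2 df, at two-sided P < 0.005:

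| True difference Δ | n=15 | n=21 |
|---|---|---|
| 0.8 SD | 22% | 37% |
| 1.0 SD | 40% | 61% |

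By the normal approximation, 80% power needs 2(2.807 + 0.842)²/Δ² per arm: 42 at 0.8 SD and 27 at 1.0 SD.

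**The case against.** The strongest reply is that this is a condensed article and the sequence may simply have been cut short. The sentence giving the paired test opens with the word *First*, and the Discussion states an intention to compare brain changes across the interventions. A between-arm step may therefore be planned and unreported. That stands as far as it goes: a reader might infer that no comparison will be made, or that the placebo arm goes unused, and the text does not show either. It shows that none is specified. But the article does not leave the imaging test open. It fixes the test, threshold and output for a primary outcome, and no second step follows.

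A reader might also infer that aim 3 as a whole cannot be answered. It can in part, because the correlations within each group are a separate, within-arm question.

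The healthy volunteers are a weaker matter. The Study design and Discussion sections say they are recruited and, for the central mechanism study, scanned; no test uses their scans. Aim 3 does not name them and no wrong test is fixed for them, so this is silence in a condensed article and not an error.

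Finally, the error rates depend on the assumed shared change: they are small when it is small, and they presuppose that someone reads the within-arm maps as a comparison, which the article does not say it will do.

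**Conclusion.** The point holds in this form: the test specified for the fMRI primary outcome is within-arm only and does not match the comparison with placebo in aim 3. As written, that part of aim 3 has no analysis that can answer it. Used in its place, side-by-side maps would suggest a drug-versus-placebo difference where none exists in 0.5% of cases with no shared change, 3.5-5.6% at 0.3 SD, 11-18% at 0.5 SD, 22-25% at 0.7 SD and 9-21% at 1.0 SD.

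These figures rest on assumed effect sizes, independent arms, two-sided testing and a single region. They ignore the 20-voxel cluster rule and are not whole-brain error rates. The mismatch itself needs none of these assumptions.

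**What to change.** In the Regional homogeneity analysis section, make the main fMRI analysis a between-arm comparison: either a group-by-time model, or an ANCOVA of post-treatment ReHo adjusted for baseline ReHo. State the contrasts in advance (each active arm versus placebo, and combination versus paroxetine) and say how multiplicity across these four is handled. Keep the paired t-tests as descriptive. As a side note, state the baseline contrast of APE patients with the 15 healthy volunteers.

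The cost is wording only: no new scans or patients. It should be settled before the data are seen. The real downside is that fewer regions will be declared, given the modest power shown above. Baseline adjustment may recover some precision, by an amount the article gives no means to estimate.

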### MRI scan

A GE3.0T magnetic resonance scanner (General Electric Company, America) at the Chongqing Traditional Chinese Medicine Hospital and a head orthogonal coil were used for 2 scans before and after treatment. A single excitation gradient echo planar imaging sequence was used for acquisition. The parameters were: TR/TE: 2000 m/30 m, FOV: 240 mm, matrix size: 64 × 64, flip angle: 90°, in-plane resolution: 3.75 mm × 3.75 mm, slice thickness: 5 mm thick with no gaps, and 32 sagittal slices.

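### The ReHo rule (P < 0.005, clusters above 20 voxels, no correction named) does not control whole-brain error for a primary outcome

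*Protocol article*

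**What the plan says.** The Abstract and the Primary outcome section of the protocol article make the change in brain fMRI a primary outcome beside IELT.

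The section Regional homogeneity analysis states the test: "First, a paired t - test was used for the comparative analysis of the ReHo images of the APE subjects in each group". That gives four before–after maps, one per arm. The search covers the whole brain: "BrainMask_61 × 73 × 61. img was selected as the whole - brain mask file". The decision rule for each map is: "The statistical threshold was set at P < 0.005, and the minimum activation cluster was required to be larger than 20 voxels". The section does not say whether P is one- or two-sided.

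The section Regional homogeneity calculation fixes what shapes the smoothness of these maps. ReHo is Kendall's concordance over a neighbourhood: "the regional homogeneity of each voxel and its 26 adjacent voxels in the same time series was calculated point - by - point". Smoothing follows: "The data were smoothed using a Gaussian kernel function with a Full - Width at Half - Maximum (FWHM) of 6 mm". One reason given for smoothing is "To ensure that the image data had the properties of a random Gaussian field to meet the statistical assumptions of SPM"; the others are noise reduction and normalization error.

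The article mentions no family-wise error, false discovery rate, random-field, permutation or simulation-based correction, no derivation of the 20-voxel extent, and no adjustment for four maps.

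**The concern.** A whole-brain map is tens of thousands of correlated tests. With about 68,375 voxels, a threshold of 0.005 in one direction lets through about 68,375 × 0.005 = 342 voxels by chance. Whether these form clusters above 20 voxels depends on how smooth the map is. A fixed extent controls error only if it was derived from that smoothness, and here it was not. The article smooths partly so that random-field assumptions hold, which is the condition for a calibrated cluster threshold, but states no such threshold.

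At stake is whether regions reported for a primary outcome can be told apart from noise. The Introduction also plans to relate brain changes to clinical improvement, and the Discussion expects stronger evidence on the central mechanism.

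**Working it through.** The protocol states no whole-brain error rate, so there is no figure to reproduce. The rate was estimated by simulation with no true effect anywhere.

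**Inputs from the protocol article**
- Rule: P < 0.005, cluster > 20 voxels; paired t-test in each of four arms (Regional homogeneity analysis).
- Grid 61 × 73 × 61 (same section).
- 27-voxel concordance, then a 6 mm kernel (Regional homogeneity calculation).
- Acquisition: "in-plane resolution: 3.75 mm × 3.75 mm, slice thickness: 5 mm thick with no gaps" (MRI scan).
- Patients per arm: "15 subjects were needed in each group, and 21 subjects were included in each group" (Study design). Both 15 and 21 were run.

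**Assumed, because not stated**
- 3 mm voxels, an ellipsoid mask of 68,375 voxels, 80 time points, 18-connectivity.
- Sidedness: three readings were run.

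**Scale of the extent.** 20 voxels × 27 mm³ = 540 mm³. One acquired voxel is 3.75 × 3.75 × 5 = 70.3 mm³, so the limit is about 540 / 70.3 = 7.7 acquired voxels.

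**Step 1: the stated pipeline on white noise.** Noise at the acquired resolution was resampled to 3 mm, turned into ReHo maps, divided by the whole-brain mean and smoothed at 6 mm. The resulting smoothness was about 7.4–7.8 mm, more than the kernel alone, because resampling and overlapping neighbourhoods add to it. There were 150 sign-flip runs per setting on 21 difference maps. Let p be the chance of at least one false cluster in one arm. The arms hold different patients, so the four-arm chance is 1 − (1 − p)^4.

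| Reading of 0.005 | n | p per arm | Four arms |
|---|---|---|---|
| One-sided, both directions tested | 15 | 0.827 | 1 − 0.173^4 = 0.999 |
| One-sided, both directions tested | 21 | 0.927 | 1 − 0.073^4 > 0.999 |
| One-sided, one direction tested | 15 | 0.627 | 1 − 0.373^4 = 0.981 |
| One-sided, one direction tested | 21 | 0.760 | 1 − 0.240^4 = 0.997 |
| Two-sided (0.0025 per direction) | 15 | 0.307 | 1 − 0.693^4 = 0.769 |
| Two-sided (0.0025 per direction) | 21 | 0.347 | 1 − 0.653^4 = 0.818 |

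The mean number of false clusters per arm is 1.9 (n = 15) and 2.4 (n = 21) in the first reading, and about 0.4 in the two-sided reading. Monte Carlo error on per-arm rates is about 2–5 points.

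**Step 2: dependence on smoothness.** Gaussian fields, 120 runs each, n = 15 and 21, both directions:

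| Smoothness (FWHM) | One-sided 0.005, per arm | One-sided 0.005, four arms | Two-sided 0.005, four arms |
|---|---|---|---|
| 6 mm | 12–14% | 39–46% | 0–3% |
| 8 mm | 94–97% | about 100% | 90–95% |
| 10–12 mm | 100% | about 100% | > 99.9% |

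The same rule moves from near 0 to near 100% on smoothness and sidedness alone.

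**Step 3: the extent that would hold about 5% per arm over both directions.** With one-sided 0.005 in each direction, this is about 39–46 voxels in the white-noise pipeline, 87–93 at 10 mm and 132–139 at 12 mm. With two-sided 0.005, it is about 29–30 in the pipeline and 56–65 at 10 mm.

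**Step 4: tightening the voxel level only.** P < 0.001 per direction with > 20 voxels still gives 8–9% per arm at 8 mm and 30–38% at 10 mm. The extent has to follow the estimated smoothness.

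**The case against.** The strongest objection is that a reader might infer that false regions are close to certain across the four arms. The article does not support that as a general statement. It gives no sidedness for the imaging test, and its only mention of a two-sided test is under Clinical variables analysis. With 0.005 two-sided, the white-noise pipeline gives 77–82% across four arms, which is high but not near certainty. A single SPM t-contrast is one-sided, which favours the higher figures but does not settle the matter. Voxel size, mask count, number of time points and smoothness are also assumed. This part stands, so the rates are given as a range.

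Other limits also stand:
- The article does not call the threshold uncorrected; this is inferred because no correction is named.
- Smoothing without a stated random-field correction is an omission, not a contradiction, since the article gives other reasons to smooth.
- Nothing says that the planned correlations will use only the clusters that pass this rule, so contaminated correlations are possible but do not follow.
- The imaging aim is partly exploratory, and IELT is untouched.

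Two defences do not stand. The 6 mm case, where the rates are lowest, is below the smoothness that the stated pipeline produces even from white noise. The point is also not merely left to a statistical analysis plan: the article states a threshold, and it governs a primary outcome.

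**Conclusion.** The concern holds in this form: the rule does not control whole-brain error, because its 20-voxel extent is not calibrated to the smoothness of the maps. This follows from the text and from the spread of rates in Step 2. The size is conditional. Under the assumptions listed, the chance of at least one false cluster is 83–93% per arm and over 99% across four arms (one-sided, both directions), 63–76% and 98–99.7% (one direction), or 31–35% and 77–82% (two-sided). White noise has no spatial correlation of its own, so real data would push these rates up. Even the lowest pipeline figure is about six times a 5% level per arm (31 / 5 = 6.2). For a primary outcome this should be corrected before the maps are analysed.

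**What to change.** In Regional homogeneity analysis, replace the rule with a voxel height of p < 0.001 and cluster-level family-wise error from SPM12 random-field theory, or use permutation inference (for example TFCE). State that both directions are covered.

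Apply it to the four planned within-group maps. The section states no between-group ReHo contrast, although the Introduction promises comparison with placebo. Any such comparison should be written in and come under the same control.

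Divide the family-wise level across the maps. At 5% per map, four maps give 1 − 0.95^4 = 18.5%. At 0.05 / 4 = 0.0125 per map they give 1 − 0.9875^4 = 4.9%. If between-group maps join the family, the divisor grows.

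Maps at P < 0.005 with more than 20 voxels may still be shown, but only as exploratory and labelled uncorrected.

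The software is already planned, so the work is a short rewrite of the section and a changed setting, plus a decision on which maps form the family. The cost is that fewer regions will pass and sensitivity to small effects falls.

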### Data monitoring and management

The Data Monitoring Committee will oversee safety and data monitoring and provide recommendations for trial design adjustments without any conflicts of interest. The Department of Urology at Chongqing Hospital of Traditional Chinese Medicine will ensure the quality of informed consent, recruit eligible participants, implement intervention measures, and manage data. Designated personnel will be responsible for collecting Case Report Forms (CRFs), as well as data transmission and analysis. Investigators and the principal investigator will be responsible for retaining all records, while the data center will store anonymized CRF data. Electronic data will be stored on password-protected computers, and all paper data will be kept in secure filing cabinets. Meanwhile, individual participant data can be accessed via the ResMan platform (Table 1).

**TABLE 1 T1:** Standard protocol items.

Study Protocol Period							
	Enrolment	Distribution	Post-distribution(week)				
Time point			1	2	3	4	5
Enrolment:							
Eligibility screen	x						
Informed consent	x						
Demographics	x						
Allocation		x					
Intervetion:							
Paroxatine			x	x	x	x	
CHSGS			x	x	x	x	
Paroxatine+CHSGS			x	x	x	x	
Placebo			x	x	x	x	
Assessment:							
ZYZHPF	x					x	
PEP	x					x	
IELT	x					x	
CIPE	x					x	
MRI	x					x	
Adverse events			x	x	x	x	Call-back

